### Biomarkers

Biomarker discovery and validation is a critical aim of the medical and scientific community.^33^ Biomarkers can be used as an objective assessment tool for health, performance, recovery and talent identification in elite sport. Among the most critical hormones for athletes seem to be cortisol, testosterone, dehydroepiandrosterone and immunoglobulin-A (Ig-A). However, testosterone to cortisol (T:C) ratio is considered to be more sensitive to training stress than either measure alone,^33^ as several studies report poor performance outcomes and suboptimal training adaptations in athletes with a low T:C ratio.^34 35^ However, to the best of the authors’ knowledge, no previous work has examined the use of biomarkers for injury prevention, recovery after an injury or identification of individuals at increased risk.

Given all of the above, there is a need for better health surveillance, load monitoring and support services with an emphasis on injury/illness prevention and rehabilitation.^36^ As DC athletes have a wider variety of loads that pose greater psychophysiological strain to them, they could also be at an increased risk for injury/illness. Therefore, more comprehensive monitoring of potential risk factors in this specific population is warranted. It is not yet known, but important to determine how much of overall load can an athlete withstand before injury/illness occurs. Thus, the primary aim of this study is to determine how specific physical, psychosocial and DC loads affect the occurrence of injuries and illnesses in elite handball players and how much of a variation in the athlete’s load leads to an occurrence of an injury/illness. A secondary aim is to determine the association between objective and subjective measures of stress as well as examine the benefits of certain biomarkers to monitor stress, load and injury/illness occurrence in athletes.

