**Figure 1 F1:**
[figure not shown]
Assessment plan. LESCA, Life Events Survey for Collegiate Athletes.

**Table 1 T1:** Questionnaires and tests

Test/questionnaire	Outcome	Purpose
**SDSCQ**	Age, sex, level of education, sport, years of training, player position, previous injuries	General information about the athlete
**Anthropometry**	Body height (cm), body weight (kg)	Measure of basic anthropometric characteristics of an athlete
**LESCA**	Major life events score	Measure of life stress
**OSTRC**	Weekly health problems (acute and overuse injuries, illnesses), measured as prevalence and incidence and severity as OSTRC-severity score and time-loss days	Identifying health problems
**Weekly load and stress**		Monitoring of athlete’s load
	Training load in hours	
	Competition load in minutes	
	Academic load in hours	
	Work load in hours	
	Average daily sleeping hours	
	Perceived stress on scale 1–10	
**Blood biomarkers**		Monitoring of stress/insufficient recovery and/or health problem risk
Cortisol	Cortisol values in nmol/L	
Free testosterone	Free testosterone values in pmol/L	
Ig-A	Ig-A values in g/L	
	Free testosterone: cortisol ratio	

LESCA, Life Events Survey for Collegiate Athletes; OSTRC, Oslo Sports Trauma Research Center Questionnaire on Health Problems; SDSCQ, Sociodemographic and Sports-Career Related Questionnaire.

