#### Life Events Survey for Collegiate Athletes Questionnaire

At the baseline and final measurements, the athletes will be asked to complete Life Events Survey for Collegiate Athletes (LESCA)^41^ in order to get more contextualised view of the life events that were happening in the past 12 months. LESCA is a 69-item questionnaire where athletes rate how each life event affected their lives in the past 12 months on a −4 to 4-point scale (−4, extremely negative to +4, extremely positive). The events include personal, academic-related and sports-related events. From summing the rated life events, two life stress scores, negative (NEG) and positive (POS) are obtained, while a total life stress score can as well be obtained by summing the NEG and POS scores together.^41^

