#### Weekly load and stress questionnaire

The teams will weekly report training and competition load for each athlete, while academic (educational activities, including lectures, exams and studying) and work load (a part-time or full-time job besides playing sports) for the past 7 days will be reported by the athletes themselves. Competition load will be reported in minutes for each game played in the past week, while training, academic and workload will be reported in hours. The athletes will additionally report average hours slept per day over the past week and rate their perceived overall stress of that week on the scale 1–10.

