### Statistical analysis

Statistical analysis will be performed using standard statistical software (SPSS V.27.0, IBM, Armonk, New York). Descriptive statistics will be used for all variables. Normality of data distribution will be assessed using the Shapiro-Wilk test. In case of non-normally distributed data, non-parametric statistics will be used, otherwise, the statistics for normally distributed data will be used. The data will be analysed using a logistic regression model to properly account for the dependency induced by the repeated observations over time within each subject. Main effect of all dependent variables on injury/illness occurrence will be studied using repeated measures analysis of variance (ANOVA) with time (preparation period vs competition period vs off-season period) as within factor, while group (injured/ill vs healthy) as between factor. Where significant effects will be found for group, time effects or two-way interactions, pairwise comparisons will be used to address the significant differences for each variable independently. For comparison of the groups, we will use independent t-test. The magnitude of effect for all dependent variables will be reported as partial eta squared (η^2^). In addition, *Cohens’ d* (ES) will be used to assess magnitude of difference between groups. Furthermore, regression analysis will be used to assess predictive power of individual parameters to identify injury/illness occurrence. For the correlation of subjective measures of stress with the objective measures, bivariate correlation will be used. Additionally, Bland-Altmann analysis will be used (low/high stress normative values) as previously recommended.^42^ Furthermore, receiver operating characteristic (ROC) curve analysis will be used for defining the cut-off values. Hypotheses will be accepted or rejected at p≤0.05.

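### The Bland-Altman analysis has no pair of measures it can apply to: the only evident pair, perceived stress against blood biomarkers, shares no quantity or unit

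*Protocol article*

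**What the plan says.** The secondary aim is given at the end of the Introduction: "A secondary aim is to determine the association between objective and subjective measures of stress". The Statistical analysis section assigns a method to it: "For the correlation of subjective measures of stress with the objective measures, bivariate correlation will be used". The next sentence adds that "Bland-Altmann analysis will be used (low/high stress normative values"), and cites an earlier recommendation for it. A sentence on ROC analysis for cut-off values follows.

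The measures are described elsewhere in the article:

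- **Subjective, weekly.** Athletes "rate their perceived overall stress of that week on the scale 1–10" (Weekly load and stress questionnaire). Table 1 lists this as "Perceived stress on scale 1–10".
- **Subjective, at baseline and end.** For LESCA, "From summing the rated life events, two life stress scores, negative (NEG) and positive (POS) are obtained", from item ratings between -4 and +4 that cover the past 12 months.
- **Objective.** Table 1 lists "Cortisol values in nmol/L", free testosterone in pmol/L, Ig-A in g/L, and the free testosterone to cortisol ratio. Its stated purpose for them includes stress monitoring. The Blood biomarkers section plans three to five sampling timepoints.

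**The concern.** Bland-Altman analysis takes the difference between two measurements of the same quantity on the same scale. It reports the mean difference (bias) and the mean difference plus or minus 1.96 SD (limits of agreement). A rating from 1 to 10 minus a concentration is not a quantity, so neither summary has an interpretation.

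The stake is how the secondary aim is reported. A published bias with limits invites the reading that perceived stress can, or cannot, stand in for a blood test in athlete monitoring. The numbers would carry no information on that question, because they change with the unit in which the laboratory reports.

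**Working it through.** The protocol states no figure for this analysis, so there is none to reproduce. The check has four steps. The documents give no means or SDs for stress or the biomarkers, so all of those below are assumptions.

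**1. Which pair is meant?** The Bland-Altman sentence names none. It opens as an addition to the subjective-objective correlation and refers to stress values. The article describes no second assay, repeat reading or second instrument that measures one quantity in one unit. The subjective-objective pair is thus the only evident candidate:

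| Subjective | Objective |
|---|---|
| Stress rating, 1-10 | Cortisol, nmol/L |
| LESCA scores, summed ratings | Free testosterone, pmol/L |
| | Ig-A, g/L |
| | Free testosterone to cortisol ratio |

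No entry on the left shares a unit with any entry on the right.

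**2. Does the result depend on the unit?** One simulated sample of 149 players (the protocol's dropout-adjusted sample size) was used. Stress had mean 5 and SD 2, truncated to 1-10. Cortisol had mean 400 and SD 100 nmol/L. The sample correlation was 0.20. The difference is stress minus cortisol.

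| Cortisol unit | Bias | Limits of agreement | Correlation |
|---|---|---|---|
| nmol/L | -398.5 | -596.9 to -200.1 | 0.20 |
| µmol/L (values divided by 1000) | +4.6 | 1.2 to 8.1 | 0.20 |

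The assumed means alone show why: 5 - 400 = -395, and 5 - 0.4 = +4.6. The players and blood samples are the same, yet the sign of the bias reverses. The correlation does not move.

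**3. What drives the limits?** With biomarker SD *b*, stress SD *s* and correlation *r*:

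Var(difference) = b² + s² - 2·r·b·s, and half-width = 1.96·√Var.

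*Cortisol in nmol/L, b = 120, s = 2.5:*
- r = 0: 1.96·√(14400 + 6.25) = 235.3
- r = 0.3: 1.96·√(14406.25 - 180) = 233.8
- r = 0.6: 1.96·√(14406.25 - 360) = 232.3
- Stress share of b² + s²: 6.25/14406.25 = 0.04%. Over b = 80 to 150 and s = 1.5 to 2.5 the share is about 0.01% to 0.1%.

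*Ig-A in g/L, s = 2.5:*
- b = 0.5: stress share 6.25/6.5 = 96%. The half-width is 1.96·√6.5 = 5.00 at r = 0 and 1.96·√5.0 = 4.38 at r = 0.6, which is 12% narrower.
- b = 1.5: stress share 6.25/8.5 = 74%. The half-width is 1.96·√8.5 = 5.71 at r = 0 and 1.96·√4.0 = 3.92 at r = 0.6, which is 31% narrower.

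So cortisol in nmol/L swamps the stress score, while the stress score dominates Ig-A in g/L. Which measure governs the limits is an accident of scale.

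**4. Would standardising help?** If both measures are converted to z-scores, the bias is 0 by construction and the limits are ±1.96·√(2(1 - r)). At r = 0.20 that is 1.96·√1.60 = ±2.48. At r = 0.674 it is 1.96·√0.652 = ±1.58. The limits depend on r alone, so they add nothing to the planned correlation.

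**The case against.** **The pair is inferred.** The sentence does not say what is compared with what, and the source it cites for its recommendation is not at hand. The bracketed reference to low and high normative values may point to a rescaled or categorised use. This stands as a caution on wording: the pairing is the only evident one but is not stated. It does not rescue the method. The bracket supplies no common unit, and categories would call for a classification-agreement measure, since Bland-Altman analysis needs continuous measurements of one quantity.

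**A reader might infer that the limits always reproduce the biomarker's spread and look the same whatever the association.** The documents do not support that in general. It is nearly true for cortisol in nmol/L, but for Ig-A in g/L the stress score dominates and the limits narrow visibly as the correlation rises. The general defect is dependence on the unit. It is also no fault of an agreement method that it does not measure association; the planned correlation has that task.

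**A reader might infer that the secondary aim is lost.** It is not. The Bland-Altman analysis is introduced as an addition, the aim is worded as association, and bivariate correlation and ROC analysis remain. The injury and illness analyses do not use it. This limits the severity.

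**A fuller analysis plan might clarify.** It might, but the article names the method for this comparison. A plan that carries it out for this pair inherits the problem.

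**Conclusion.** Wrong as written; should be fixed. For the only evident pair, the measures share neither quantity nor unit and no conversion is stated, so the bias and limits of agreement would be set by the laboratory unit. In the illustration, the bias moves from -398.5 to +4.6 on a change of unit alone.

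The conclusion rests on reading the sentence as applying to subjective against objective stress measures. It does not rest on the assumed means and SDs, which affect only the size of the illustration. The consequence is confined to a supplementary analysis of a secondary aim. The primary analyses, the sample size and the data collected are untouched.

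**What to change.** - **Delete** the Bland-Altman analysis for subjective against objective stress measures. If another pair was intended, name it, with its common unit.
- **Association.** Use a method that respects the three to five samples per player: a repeated-measures correlation, or a mixed model of each biomarker on perceived stress. This would replace or supplement the bivariate correlation. It has to be written in, because the repeated-measures methods now in the Statistical analysis section concern injury and illness and not this pair.
- **Low/high question, if kept.** Cross-classify high/low perceived stress against high/low biomarker at each sampling occasion. State the cut-offs for the rating and for each biomarker in advance, and report kappa with a bootstrap interval that resamples players. Do not report sensitivity and specificity unless one measure is named as the reference; the article names none.

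Cost: deletion removes one sentence, and the replacement needs a few lines of analysis text. No change to data collection or sample size is needed.

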**Methods and analysis:**

This prospective cohort study, as part of a PhD project, will be carried out on 200 elite handball players of first men's handball league in Slovenia during an entire handball season, lasting from July 2022 to June 2023. Primary outcomes, including health problems, loads and stress, will be assessed weekly on a player level. Other player-related outcomes will include anthropometry, life event survey and blood biomarkers (cortisol, free testosterone and Ig-A), which will be taken three to five times across the observation period according to the players’ training cycle.

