### Participants and sample size

A power analysis was a priory determined using the G*Power software.^38^ Based on previous studies with similar design, we expected to find nearly two times as high odds of injury occurrence in athletes during a period of high academic stress compared with low academic stress (OR=1.78; effect size (ES)=0.14)^25^ with power of 0.90 and α=0.05, two-tailed, which calculated an initial sample size of 134 participants. As in sports practice, the athlete drop-out is to be expected (due to travelling, international transfer to another club/state, etc); we adjusted the originally calculated sample size by following formula: N1=n/(1−d),^39^ where N1 is adjusted sample size, n is the sample size required as per the proposed formula (N=134) and d is the drop-out rate (d=0.10). This resulted in total sample size of 149 athletes. Inclusion criteria will be as follows: DC and non-DC registered male handball players who are competing in the first Slovenian handball league and are above 18 years of age.

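### ROC cut-offs come from the only cohort described, with no internal validation named, so accuracy reported at them will be optimistic and the cut-offs themselves imprecise

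*Protocol article*

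**What the plan says.** The ROC step has one sentence in the Statistical analysis section: "receiver operating characteristic (ROC) curve analysis will be used for defining the cut-off values". It does not say which marker, which outcome unit (athlete, athlete-week or sampling timepoint) or which criterion picks the cut-off. In the same section, "regression analysis will be used to assess predictive power of individual parameters to identify injury/illness occurrence".

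Half of the primary aim, stated at the end of the Introduction, is to find "how much of a variation in the athlete’s load leads to an occurrence of an injury/illness". ROC analysis is the only listed method that yields a threshold.

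The Study design section describes a single cohort over one 46-week season. No second cohort, hold-out sample, cross-validation or resampling appears among the listed methods. The planning effect is "OR=1.78; effect size (ES)=0.14". The sample size section ends with "This resulted in total sample size of 149 athletes", while the abstract says that the study "will be carried out on 200 elite handball players".

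**The concern.** A cut-off picked because it separates cases from non-cases best in a sample has partly been fitted to that sample's noise. Sensitivity and specificity computed at that point in the same data are biased upward, and the cut-off moves a good deal from sample to sample. Both effects are strongest when the marker is weak and the cases are few. Screening several candidate markers and reporting the best one adds a further layer of optimism.

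This matters because the article expects direct use of the results in sports and clinical practice and foresees policy recommendations. A threshold whose discrimination is overstated, or that could have landed elsewhere in another season, would be passed to teams with unwarranted confidence.

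**Working it through.** **The plan's own figure.** The article gives no figure for cut-off accuracy. Its only related calculation is the sample size: 134/(1 − 0.10) = 148.9, rounded up to 149, which agrees. The starting figure of 134 is not tied to a named test. A repeated-measures ANOVA with f = 0.14, two measurements and correlation 0.5 (assumed) gives 136, so I take 134 as given. It was not sized for ROC work.

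**Inputs.**
- N = 149 (Participants and sample size) and N = 200 (abstract).
- OR = 1.78 (Participants and sample size).
- Case share 20% and 45%: an assumption, borrowed from the prevalence range in the Introduction. It is not a design input.
- Assumed: equal-variance normal marker, one record per athlete, cut-off at the maximum of the Youden index J = sensitivity + specificity − 1.

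**Planning effect as an AUC.** d = ln(1.78) × √3/π = 0.318. AUC = Φ(d/√2) = Φ(0.225) = 0.589. The best attainable J is 2Φ(d/2) − 1 = 2Φ(0.159) − 1 = 0.126.

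**Simulation (3000 runs per row).** Apparent J is computed in the sample that chose the cut-off. True J is the population value at that same cut-off. Ratios come from unrounded values. The last column is in within-group SD of the marker.

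| N | Cases | AUC | Apparent J | True J | Ratio | Central 90% of cut-off around optimum |
|---|---|---|---|---|---|---|
| 149 | 20% | 0.589 | 0.221 | 0.108 | 2.03 | −0.95 to +1.07 |
| 149 | 45% | 0.589 | 0.199 | 0.111 | 1.80 | −0.94 to +0.91 |
| 200 | 20% | 0.589 | 0.205 | 0.111 | 1.85 | −0.90 to +0.93 |
| 200 | 45% | 0.589 | 0.189 | 0.113 | 1.68 | −0.86 to +0.82 |
| 149 | 20% | 0.70 | 0.366 | 0.269 | 1.36 | −0.64 to +0.73 |
| 200 | 45% | 0.70 | 0.338 | 0.275 | 1.23 | −0.56 to +0.53 |
| 149 | 20% | 0.80 | 0.513 | 0.428 | 1.20 | −0.48 to +0.58 |
| 200 | 45% | 0.80 | 0.490 | 0.436 | 1.12 | −0.42 to +0.41 |

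Under this model a case share of 1 − 0.20 = 80% mirrors 20%, so a higher season-long share does not by itself remove the effect.

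**What the imprecision means.** At the planning effect, a cut-off 0.9 SD below the optimum has specificity Φ(0.159 − 0.9) = Φ(−0.741) = 0.23. One 0.9 SD above it has Φ(0.159 + 0.9) = Φ(1.059) = 0.86.

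**On another scale.** Balanced accuracy is (1 + J)/2. In the first row it is 0.611 apparent against 0.554 true, an inflation of 10%. In the fourth row it is 0.595 against 0.557, about 7%.

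**Athlete-weeks as rows.** 149 × 46 = 6854 rows, or 3427 if half are completed. With a 20% case share and AUC 0.60, apparent J is 0.152 to 0.155 against 0.139 to 0.140, a ratio of 1.09 to 1.12. At AUC 0.70 the ratio is 1.03 to 1.05. Clustering within athletes is ignored, so these are lower bounds.

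**Several markers.** Table 1 lists ten candidates: six weekly load, sleep and stress items, three biomarkers and one ratio. For one null marker at N = 149 the mean apparent J is 0.10 to 0.12. For the best of ten independent null markers it is 0.19 to 0.23 at N = 149 and 0.16 to 0.20 at N = 200, close to a real marker at the planning effect.

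**The case against.** The strongest reply is that this is silence, not error. The article says only that ROC analysis defines cut-offs. It names no Youden criterion and no choice among markers, and it does not say that accuracy will be reported at the cut-off. Validation detail may sit in a fuller plan. A reader might infer that the plan has accuracy judged on the same athletes, but that is an inference: only one cohort is described, and the text does not say how the cut-offs will be assessed. This lowers confidence in the size of the bias. It does not remove the point, because an imprecise cut-off follows from the stated method whether or not accuracy is reported.

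The purpose of the ROC step is also uncertain. Its sentence follows the one on Bland-Altman analysis of low and high stress values, so it may concern stress thresholds and not load or biomarkers. This stands, though the same optimism would apply to any marker cut there.

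The unit of analysis matters as well. Load and health problems are recorded weekly, and with athlete-weeks the optimism nearly vanishes for all but very weak markers. This stands for load. It does not carry over to the biomarkers, sampled three to five times, or to the life-events survey, completed twice. The comparison of injured/ill with healthy players also reads as a classification of athletes.

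Finally, a reader might infer that groups split at the optimal cut-off will be tested and so lose the 5% error rate. The article does not support this. Its groups are defined by injury or illness, and no test of a dichotomised marker is planned. Its regression step also leaves room for inference on the continuous predictor.

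**Conclusion.** The point holds in a limited form. Cut-offs defined by ROC analysis in a single cohort, with no internal validation named, will carry optimistic accuracy and wide uncertainty. At the planning effect, with one record per athlete and 149 to 200 athletes, the apparent Youden index overstates the true 0.11 by about 0.08 to 0.11, and the cut-off has a central 90% range of about 0.8 to 1.1 SD either side of its optimum.

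A reader might infer that the thresholds will in general look twice as accurate as they are. The calculations do not support that. A ratio near two appears only on the Youden scale and only for a weak marker at athlete level. It is about 1.2 to 1.4 at AUC 0.70 and 1.1 to 1.2 at AUC 0.80, and balanced accuracy is inflated by about 10% at most in the settings tabulated. The AUC of one marker named in advance is not inflated by choosing a cut-off.

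The sizes rest on an assumed case share, the equal-variance normal model, the Youden criterion and no modelling of clustering. The direction of the bias is not in doubt; its size is conditional.

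**What to change.** Keep the ROC step and add four things.

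1. State the marker, the outcome unit and the criterion that picks each cut-off.
2. Bootstrap whole athletes, keeping all of an athlete's rows together. Repeat the cut-off selection, and any selection among markers, in each resample.
3. Report optimism-corrected sensitivity and specificity, with a bootstrap interval for each cut-off. Correct the AUC only if markers are selected or combined.
4. Label the cut-offs exploratory pending validation in another cohort.

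The cost is a short piece of analysis code and less favourable reported accuracy. Data collection and the planned sample size stay as they are.
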